## Methods/Design

### Study design

The study is designed as dual**-**center, randomized controlled trial with three arms and follow**-**up assessment (see Figure 1). The study procedure is implemented at the Department of Gynecology, Gynecological Endocrinology and Oncology, Philipps University Marburg, Germany, and at the University Medical Center Hamburg**-**Eppendorf, Germany. Participants are women with hormone**-**receptor**-**positive breast cancer, scheduled to start adjuvant endocrine treatment. After signing informed consent to participate in the study and receiving medical information about endocrine treatment from the hospital staff, all patients are provided additional standardized information and patient education about the scheduled treatment by a trained research assistant/ clinical psychologist to homogenize knowledge about endocrine treatment. The structured treatment information is given verbally and through a leaflet, illustrating the physical mode of action, the desired effects, and the potential side effects of endocrine therapy. After completing baseline assessment (including symptom status and pre**-**treatment side**-**effect expectations) patients are randomly assigned to one of three groups. Group 1 receives standard medical care (SMC) only. Group 2 receives SMC and the side**-**effect prevention training (SEPT). Group 3 receives SMC and supportive therapy as an attention control group (ACG). Outcomes are assessed homogeneously in all three groups, three and six months after the start of medication intake.

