### Sample size calculation

Required sample sizes were determined a priori with G**-**Power [37]: The sample size for the randomized group comparison was determined according to a MANOVA with repeated measures, testing for a three groups x three time points interaction. Assuming a medium effect size of f(V)=.20, N=153 patients (n=51 per group) are needed to achieve 80% power.

Taking into account a potential drop**-**out rate of 20% (e.g., due to exhaustion or medical complications), we aim to include a total of 184 breast cancer patients.

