### Quality standards (Minimization of bias)

#### Randomization and blinding

Randomization follows after completing baseline assessment. Patients are equally allocated to one of the three treatment arms using sealed envelopes. Assignment follows a stratified permuted block randomization procedure with a block size of nine. Stratification criteria (2×2) are the sum score (≤13 vs. >13) of the hospital anxiety and depression questionnaire (HADS**-**D) [38,39] during hospital stay and type of medication (aromatase inhibitor vs. tamoxifen). Assignment sequence is generated by staff who are not involved in the intervention process and conducted electronically using the statistical program WINPEPI [40]. The research assistants responsible for the assessment are blinded to group allocation.

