### Data analysis

Missing values will be replaced using multivariate imputation techniques. A repeated measures multivariate analysis of variances (MANOVA) will be used to analyze treatment effects. To identify predictors of treatment outcome, multiple regression analyses will be conducted. To analyze pathways of the effects, mediator analyzes will be computed. Case studies will be performed to illustrate characteristics of the treatment processes from patients’ und therapists’ perspectives. Level of significance will be set at α = .05.

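### Randomisation is stratified by HADS-D score and medication type, but the stated MANOVA names no stratum term; to the extent the strata predict change in side effects, the test is conservative and loses some power

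*Protocol article*

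**What the plan says.** The section on randomization and blinding in the protocol article describes permuted blocks of nine within a 2×2 stratification. One factor is the HADS-D sum score, cut at 13, taken "during hospital stay and type of medication (aromatase inhibitor vs. tamoxifen") being the other.

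The data analysis section gives the treatment-effect model in one sentence: "A repeated measures multivariate analysis of variances (MANOVA) will be used to analyze treatment effects". It names no covariate, stratum or centre term. The sample size section describes the powered test as "testing for a three groups x three time points interaction", again with no further factor.

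Table 2 measures GASE at baseline and at three and six months, which fits the three time points. It lists HADS as a process variable, measured repeatedly. Its control variables are somatosensory amplification, prior endocrine experience, partnership quality and additional medication; type of endocrine medication and centre are not among them.

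The study design section describes a dual-centre trial, at "Philipps University Marburg, Germany, and at the University Medical Center" in Hamburg. Centre is not a stratification factor.

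**The concern.** Stratified allocation makes the arms more alike on the stratification factors, so the true sampling variance of the group contrasts falls when those factors predict the outcome. A model that omits the factors does not register this. It leaves their variance in the residual, reports standard errors larger than the actual variability of the estimates, and tests below the nominal level. The price is power, not validity.

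The precision at stake comes from variables that are already recorded and on which the allocation already conditions.

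**Working it through.** **Inputs from the article.** Three groups, three time points; "Assuming a medium effect size of f(V)=.20"; "N=153 patients (n=51 per group) are needed to achieve 80% power"; "Level of significance will be set at α = .05". The baseline data section gives 30.9% on an aromatase inhibitor and 69.1% on tamoxifen among the first 55 women.

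**Assumed.** R² is the share of variance in the within-patient change contrasts explained by the strata. The article gives no value, so 0 to 0.20 is shown.

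**Step 1: reproduce the plan's figure.** For the within-between interaction with k=3 groups and m=3 times, using Pillai's V:
- s = min(k−1, m−1) = 2
- df1 = (k−1)(m−1) = 4
- df2 = s(N − k − (m−1) + s) = 2(N − 3), which is 300 at N=153
- λ = N·s·f(V)² = 153 × 2 × 0.04 = 12.24

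The noncentral F gives power 0.804 at N=153. The smallest N reaching 80% is 152, and 153 is the next multiple of three. The stated figure reproduces.

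**Step 2: add the strata.** Three degrees of freedom for the 2×2 strata give df2 = 2(153 − 3 − 3) = 294. Removing the explained variance scales the effect size to f(V)/√(1−R²), so λ = 12.24/(1−R²): 12.88 at R²=0.05 and 13.60 at R²=0.10.

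| Assumed R² | Unadjusted SE too large by factor 1/√(1−R²) | Power with strata, N=153 | N for 80% power |
|---|---|---|---|
| 0 | 1.00 | 0.804 | 152 |
| 0.02 | 1.01 | 0.813 | 149 |
| 0.05 | 1.03 | 0.826 | 145 |
| 0.10 | 1.05 | 0.849 | 137 |
| 0.20 | 1.12 | 0.892 | 122 |

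The comparator without strata is 0.804. For R² of 0.05 to 0.10 the gain is 0.826 − 0.804 = 0.022 to 0.849 − 0.804 = 0.045, equivalent to 152 − 145 = 7 to 152 − 137 = 15 patients.

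**Step 3: check by simulation.** N=153, blocks of nine within 2×2 strata, 30.9% on an aromatase inhibitor, HADS split evenly (assumed), two change contrasts correlated 0.5 before the strata effect is added (assumed), and Pillai's test with and without strata. There were 6,000 replicates under the null and 3,000 under an alternative.

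| R² | Type I error, unadjusted | Type I error, adjusted | Power, unadjusted | Power, adjusted |
|---|---|---|---|---|
| 0 | 0.049 | 0.050 | 0.76 | 0.76 |
| 0.05 | 0.047 | 0.052 | 0.76 | 0.79 |
| 0.10 | 0.035 | 0.046 | 0.74 | 0.81 |
| 0.20 | 0.029 | 0.049 | 0.75 | 0.86 |

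The Monte Carlo standard error of a 5% rate is √(0.05 × 0.95/6000) = 0.003. The alternative was not calibrated to f(V)=0.20, so these power values should be compared only with each other. They confirm the direction: the unadjusted test is conservative when the strata predict change and loses nothing when they do not.

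**Step 4: margin.** The article allows for a drop-out "rate of 20% (e.g., due to exhaustion or medical complications"). Of 184 patients, 184 × 0.8 = 147 would then complete, where power is 0.786 without the strata, and 0.809 (R²=0.05) or 0.832 (R²=0.10) with them.

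**The case against.** **Silence is not exclusion.** The data analysis section is a single paragraph. It does not say that the model is unadjusted, and a power calculation without covariates is ordinary. The full protocol or analysis plan may add the strata. This stands: the point concerns the model as the article states it and cannot be read as a decision to omit the strata.

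**A stratum effect that is constant over time cancels.** The planned test is on within-patient change, so only stratum by time effects matter. This is correct in general and is why R² is defined on the change contrasts. It is weaker for medication type. Outcomes are measured three and six months after intake starts, and the discussion section says that women who start endocrine therapy before baseline are not included. Any difference in side effects between tamoxifen and aromatase inhibitors would therefore arise after baseline. For HADS, the background says only that anxiety and depression may be relevant to nocebo and non-specific side effects. Neither effect is quantified.

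**Centre.** A reader might infer that leaving out centre also makes the standard errors too large. It does not. That argument applies only to factors used in the allocation; without stratification by centre, the unadjusted standard error and type I error remain valid. Adjusting for centre could only improve efficiency or address a chance imbalance.

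**Baseline GASE.** Adding it as a covariate is tempting, but baseline is already one of the three repeated measurements. It cannot be both outcome and covariate in the same MANOVA.

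**Conclusion.** The point holds in conditional form. The article stratifies by HADS-D score and medication type and states a group by time MANOVA with no stratum term. Followed as written, that analysis is conservative whenever the strata predict change in GASE. The loss is about 2 to 4.5 percentage points of power at N=153 for an assumed R² of 0.05 to 0.10, and nil at R²=0.

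A reader might infer that precision is certainly lost, or that the trial's error rate is compromised. The documents support neither: they give no R², and any error runs in the conservative direction, so a positive result would not be called into question. This is a free improvement to the stated model, of modest size.

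**What to change.** State that the treatment-effect model includes the HADS stratum and medication type. If the repeated measures form is kept, include their interactions with time, because stratum main effects alone do not sharpen a group by time test.

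Use the HADS value on which the patient was randomised. That value comes from the hospital stay, whereas baseline assessment is placed about two weeks after surgery and HADS is measured again after the intervention, so the wording should say which one is meant.

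Baseline GASE should enter as a covariate only if the model is recast on the follow-up values. Centre may be added in the same way as the strata, for efficiency and chance imbalance.

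The cost is a change of wording and three degrees of freedom per contrast for the full 2×2 strata, plus one if centre is added. At R²=0 the strata leave power at 0.804. No new data, procedures or patients are needed.

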#### Attrition bias

In order to examine potential attrition bias, drop**-**out analyses will be performed. In accordance with the intention**-**to**-**treat principle, the data of all patients randomised to the treatment groups will be analysed.

#### Control for therapeutic allegiance

To ensure the comparability of treatments, treatment dose, application and assessment occasions for SEPT and ACG will be identical.

All therapists are clinical psychologists with advanced cognitive behavioral training and have comparable professional experience. They are trained in the use of the treatment manual before the trial starts. Training includes a full treatment cycle with at least one patient per treatment group using video feedback and professional supervision of each treatment session. During the whole study therapists are under ongoing supervision by highly experienced psycho**-**oncologists. Both types of interventions are manualized and each therapist will treat a comparable number of patients in each group. Treatment fidelity is assessed and rated before approval of therapists to start in this trial. All sessions will be videotaped and an amount of 33% will be selected randomly and rated by an independent rater.

### Psychological interventions

In the intervention groups three individual sessions of 50–75 minutes are being held with a clinical psychologist over the course of three to four weeks (see Figure 2). One, three and six months after the intervention booster telephone calls will be made in both intervention groups.

**Figure 2 F2:**
[figure not shown]
Intervention schedule.

#### Intervention: side-effect prevention training

The goal of SEPT is the prevention of non**-**specific and nocebo side effects from endocrine therapy by optimizing treatment**-** and illness**-**related expectations. Contents of the training are psychoeducation [41] to provide a realistic view of the treatment, imagination**-**training to integrate positive aspects of medication into daily life and side**-**effect management [42] to enhance expectations about individual coping abilities. All intervention components and goals are listed in Table 1. SEPT is a manual**-**based program. Individual topics are adapted specifically to each patient according to her individual expectations. The baseline questionnaires are used as a starting point for tailoring the intervention so it is consistent with the written treatment guidelines. Patients in the SEPT group receive a booklet with patient material detailing the contents, goals and interventions of each session. The booklet also contains work sheets, postcards and further material that can be personalized by each participant. Sessions will focus on subsequent topics:

**Table 1 T1:** Intervention components and goals of the side-effect prevention training

**Intervention components**	**Goals**
**Session 1**	
- Psychoeducation about AET	- Knowledge about AET and nocebo effect
- Guided imagination and visualization of positive treatment aspects	- Strengthen control and benefit expectations
- Psychoeducation about nocebo and non-specific side effects	- Integration of positive aspects of AET into daily routines
**Homework**	
- Practice relaxation and imagination (anchored by CD)	
- Further creative work with imagination, e.g., painting	
**Session 2**	
- Develop individual problem-solving scheme for the three most important side effects	- Optimize coping expectations
- Create an action plan for behavioral and cognitive strategies	- Reduce specific concerns
**Homework**	
- Complete and modify the personal problem-solving scheme	
- Create an individual “tool box”	
- Practice relaxation and imagination (anchored by CD)	
**Session 3**	
- Psychoeducation about doctor-patient communication	- Optimizing coping expectations
- Develop distraction strategies of for the time of AET intake	- Improving patient-physician communication
- Summing up and outline treatment goals	
**Homework**	
- Practice relaxation and imagination (anchored by CD)	
- Complete and modify the personal problem-solving scheme and the tool box	
**Telefone booster calls**	
- Compare expected and occurred side effects	- Maintain optimized expectations
- Check practicability of the coping strategies and the “tool box” and modify if necessary	

Notes: *AET* = Adjuvant endocrine therapy

*Session 1:* At the beginning of the first session, psychoeducation about the active principle of endocrine treatment is given, tailored to the individual patient’s needs. The adverse side effects most expected by the patient are discussed and contrasted with treatment benefits.

A guided imagination is performed to visualize the positive aspects (e.g., protection from cancer recurrence) of the endocrine treatment. The imagination is recorded on audio file and incorporated into patients’ daily handling of the medication. Furthermore, the impact of expectations on side effects (e.g., pain following negative expectations but without the administration of any inert substance) is discussed and the concept “nocebo phenomenon” explained to the patients.

*Session 2:* Session two focuses on the development of coping strategies for side-effect management that are implemented in a written problem**-**solving scheme for the three most expected or dreaded side effects. Strategies employed include behavioral techniques, cognitive strategies, dietary advice, physical exercises, identification and avoidance of triggers for specific side effects. Patients are asked to create a “tool**-**box” at home filled with useful material to implement the discussed coping**-**strategies.

*Session 3:* This last session includes skills training for improved patient**-**physician communication to positively influence expectations about breast cancer check**-**ups. Additionally, the role of attention for the development of non**-**specific side effects and the worsening of specific side effects is discussed. Patients are encouraged to re(activate) individual resources and activities helping to distract from the potential occurence of side effects, but also strenghten the patient for the time of medication intake. At the end of the session, all topics of the previous sessions are reviewed.

*Booster calls:* The three phone calls focus on repeating the contents of the intervention. The therapeutic contact is used to give support to the patients during the first time of medication intake. Many patients describe it as very helpful to talk about their concerns in this phase of illness and treatment (the phase of rehabilitation after being discharged from hospital). During the booster calls, possible problems with the relaxation and imagination training are discussed and resolved whenever possible. The coping strategies are reviewed and adapted. Furthermore, the problem**-**solving scheme will be extended to further side effects including new coping strategies.

### Attention control group (ACG): *supportive therapy*

Supportive therapy serves as an attention control group for non**-**specific factors such as therapist’s attention and patient**-**therapist relationship. It serves to distinguish specific effects of SEPT from psychological placebo effects [43]. Supportive therapy [44] as a manualized, non**-**specific psychological intervention has been previously used in clinical trials [45]. It includes common factors such as elicitation of affect, treatment context, empathy, reflective listening, and feeling understood. It will be delivered in the same frequency and on the same occasions as SEPT (three individual sessions and three booster calls).

*Sessions 1, 2 and 3:* In the supportive therapy session contents may vary; there are no specific topics therapists need to address, there is no patient material and no homework. Nevertheless, every session can be structured into three phases: the beginning, the therapeutic dialog and the end. At the beginning patients are asked about relevant themes they want to talk about. During the therapeutic dialog patients lead the session and the therapist follows, while concentrating especially on the validation of patients’ affects. It is suggested to talk about any topics that appear to have an affective valence to the patients. The therapist focuses on creating a warm atmosphere and shows empathy and unconditional positive regard towards the patient. At the ending of all sessions all themes are reviewed with the focus on the affect of the individual patient.

In the control group booster calls are conducted simultaneously to those in the intervention group, but they do not follow a particular structure. Patients are asked about their feelings since the last session.

### Measures

Assessment occurs at four measurement points (see Table 2): at baseline approximately two weeks after surgery, after the intervention (post**-**intervention), and three and six months after the start of medication intake (follow**-**up). Questionnaires are applied by blinded research assistants at all measurement points. The following demographic and medical information will be obtained from medical charts and by baseline**-**interviews: socio**-**demographic status, age, BMI, health status, accompanying illnesses and medication (e.g., osteoporosis and medication), prior experiences with endocrine treatment (hormone contraception, hormone replacement therapy), stage of disease and tumor characteristics (UICC**-**stage, TNM**-**classification, Grade, ER/PR status, Her**-**2**-**status), type and course of primary treatment (breast**-**conserving surgery, mastectomy, radiotherapy, systemic treatment). Medical follow**-**up data include health and disease status, accompanying illnesses and medication for clinical outcome. All data will be validated and a plausibility check**-**up will be conducted.

**Table 2 T2:** Study measures

		**Baseline pre-intervention**	**Post-intervention**	**Follow-up (3 and 6 months after AET intake)**
Inclusion criteria	**Interview measures**			
	Structured psychiatric interview (mini-dips)	x^1^		
	Demographic and medical data	x		
	**Questionnaire measures**			
Primary + Secondary Outcomes	Physical symptoms and side effects + coping (GASE+Coping)	x		x
	Quality of life (EORTC QLQ C30 & BR23)	x		x
	Adherence (MARS-D), Adherence Intention	x	x	x
Expectation Scales	Expected side effects + expected coping (GASE-Expect + * *Coping)	x	x	x
	Illness beliefs (IPQ-B)	x	x	x
	Beliefs about medicines (BMQ-D)	x	x	x
Process Variables	Fear of progression (PA-F-K)	x	x	x
	Anxiety and depression (HADS)	x	x	x
	Knowledge hormone receptor	x	x	x
	Treatment evaluation		x^2^	
Control Variables	Somatosensory amplification (SSAS)	x		
	Prior experiences with endocrine treatment	x		
	Partnership quality	x		
	Additional medication	x		x

Notes:

^1^The psychiatric interview is conducted prior to the measurement to check the inclusion criteria.

^2^Completed after every therapy session in the intervention groups only.

#### Primary outcomes

*Side effects* will be measured with the General Assessment of Side Effects scale (GASE) [46,47] which systematically assesses incidence and intensity of the 36 most common side effects. To assess the most frequent patient**-**reported adverse side effects from endocrine treatment the scale was modified by adding nine further symptoms (decreased interest in sex, weight gain, feeling of tension in breast, mood swings, abdominal bloating, vaginal dryness, bone fracture, pain during sexual intercourse, cataract) resulting in a total of 45 symptoms. Patients will be asked to rate the intensity of each listed bodily complaint during the past seven days on a four point Likert scale (0 = “complaint not present”; to 3 = “severe intensity”). Additionally, patients will indicate whether they attribute each of the present symptoms to current drug intake. It shows satisfactory psychometric properties [46].

#### Secondary outcomes

*Quality of life* will be assessed with the European Organization for Research and Treatment of Cancer Quality of Life Questionnaire (EORTC QLQ**-**C30) with breast module (QLQ**-**BR23) [48]. This questionnaire can be seen as the standard multidimensional instrument to measure quality of life among cancer patients. The QLQ**-**C30 consists of five functional scales, nine symptom scales and a global quality**-**of**-**life scale. The breast module is composed of eight breast cancer specific scales including four functional and four symptom scales. Both questionnaires have demonstrated good psychometric properties [48,49].

*Coping ability* measures the perceived ability to manage occurring side effects. It will be accessed via a modified version of the GASE [46,47] that will ask patients to rate their coping ability for each of the 45 listed side effects (i.e., “How good is your ability to manage the occurring adverse symptom?) on a Likert scale from 0 = “good” to 4 = “bad”.

*Medication adherence* will be measured with the German version of the Medication Adherence Report Scale (MARS) [50,51]. This scale gives an indication of the extent to which non**-**adherent behaviors occur, including how often patients have consciously not taken their medicines or forgotten to take them. It has been used to measure the adherence in endocrine treatment before [52]. Additionally, the *adherence intention*, the *actual adherence* and the *attitude towards* in cursive will be assessed with three single items.

